## Endpoints

### Primary endpoint – ACT HIV (main trial)

The primary endpoint of the main trial is overall survival, i.e. the time from randomisation to death, during a follow-up period of 12 months. Survivors known to be alive at 12 months will be censored at that time-point and subjects who withdrew or were lost to follow-up before 12 months will be censored at the date they were last known to be alive.

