### Secondary endpoints – ACT HIV (main trial)

The secondary endpoints of the main trial are as follows:

a)Neurological disability at day 30 from randomisation, monthly until completion of anti-tuberculous drugs, and at months 12, 18 and 24. The main endpoint is the 12-month assessment and subjects who died before 12 months will be treated as having a score of 6 (‘dead’). Neurological disability will be assessed by the modified Rankin score (
Table 1).b)Time to first new neurological event or death during a follow-up period of 12 months. A neurological event is defined as a fall in Glasgow Coma Score (GCS) by ≥2 points for ≥2 days from the highest previously recorded GCS (including baseline), or the onset of any of the following clinical adverse events: cerebellar symptoms, focal neurological signs, or seizures.c)Time to neurological IRIS events from randomisation until 6 months. We will follow the International Network for the Study of HIV associated IRIS (INSHI) case definition of IRIS (
14,
Supplementary File 2). Rate of neurological IRIS is defined as the number of IRIS events divided by the observed person-time of follow-up in each treatment group. d)Time to new acquired immunodeficiency syndrome (AIDS)-defining event (as per World Health Organisation classification) or death, during a follow up period of 12 months.e)Time to HIV-associated malignancy from randomisation until 12 months. Rate of HIV-associated malignancy is defined as the number of events of the three major HIV-associated malignancies (Kaposi sarcoma, high grade B-cell non-Hodgkin lymphoma and invasive cervical cancer) divided by the observed person-time of follow-up in each treatment group. f)Serious adverse events until 12 months. Comparison of the frequency of serious adverse events between treatment groups will form an important part of the study analysis.g)Endpoints assessed at 24 months of follow up. All participants will continue to be followed up for 24 months and the following outcomes will be reported once this period has been completed for all participants: overall survival until 24 months, neurological disability at 24 months, recurrence of TBM until 24 months, time to new AIDS defining event or death until 24 months, and rate of HIV-related malignancy until 24 months.

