## Adverse events and safety reporting

### Adverse events

Specific procedures will be followed when notifying and reporting adverse events (AEs) or adverse reactions (ARs). The definitions of the EU Directive 2001/20/EC Article 2 based on the principles of ICH good clinical practice (GCP) apply to this trial protocol. All AEs and ARs will be assessed as to whether they are serious or not. If the event is serious and not only related to TBM, or is fatal, then a serious adverse event (SAE) form must be completed and the OUCRU CTU notified within 24 hours. All AEs and ARs (serious and non-serious) should be graded using toxicity gradings.

Causality of all SAEs or serious adverse reactions (SARs) in relation to the trial therapy (dexamethasone) will be assessed. There are five categories: unrelated, unlikely, possible, probable, and definitely, related. If the causality assessment is unrelated or unlikely to be related, the event is classified as an SAE. If the causality is assessed as possible, probable or definitely related, then the event is classified as an SAR. If there is at least a possible involvement of the trial treatment (or comparator), the investigator must assess the expectedness of the event. An unexpected adverse reaction is one not previously reported in the current Summary of Product Characteristics (SPC) at the time the event occurred, or one that is more frequent or more severe than previously reported. If a SAR is assessed as being unexpected, it becomes a suspected unexpected serious adverse reaction (SUSAR). Investigators should always check the current version of the SPC.

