## Statistical analysis

### Sample size justification – ACT HIV (main trial)

A previous trial of dexamethasone included 545 subjects with TBM and reported a reduced risk of death by 9 months associated with dexamethasone (hazard ratio of death 0.69 (95% CI 0.52–0.92)) and no evidence of heterogeneity with respect to HIV status though the number of HIV-infected patients was low (98 subjects) and none of them received antiretroviral therapy
^8^. A recent TBM trial of intensified TBM treatment reported 9-month mortality in 349 HIV-infected patients of 40% in both study arms and all subjects received dexamethasone
^7^. Few additional deaths are expected to occur between months 9 and 12
^15^. Assuming a target hazard ratio of 0.69 (corresponding to a mortality reduction from 52% to 40% in favour of dexamethasone), a total of 229 deaths need to be observed during the 12-month follow-up duration to obtain a power of 80% at the two-sided 5% significance level according to Schoenfeld’s formula. To achieve this and allowing for a 5% loss-to-follow-up, a total of 520 HIV-infected subjects with TBM need to be recruited into the main trial.

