### Analysis of adverse events

The number of patients with any adverse events and specific events, respectively, will be summarised and informally compared between the two treatment arms based on Fisher’s exact test. The total number of adverse event episodes per patient will also be summarised and informally compared based on a quasi-Poisson regression model with treatment as the only covariate. The following subgroups of adverse events will also be separately summarised: grade 3&4 adverse events; serious adverse events; serious adverse events possibly, probably, or definitely related to the study drug; adverse events leading to TB treatment or ART interruptions. Grade 3&4 laboratory abnormalities will be summarised in the same way as clinical adverse events.

Adverse events due to DILI will be recorded for the DILI study but also for the primary intervention (dexamethasone or placebo). An increased number of adverse events in DILI arms 1 and 2 are not expected, but if they do occur these adverse events will be associated with both the DILI randomisation strategy and for the primary intervention arm in which they occurred.

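### The overall SAE comparison includes every primary-endpoint death with no fatal/non-fatal split, so at the planned mortality it is mostly deaths and can offset or dilute non-fatal serious harm

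*Protocol article*

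**What the plan says.** Three parts of the protocol article combine.

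- **Filing rule (Adverse events).** "If the event is serious and not only related to TBM, or is fatal, then a serious adverse event (SAE) form must be completed". A fatal event is always filed. A non-fatal serious event is filed only if it is not purely a consequence of TBM.
- **Endpoint (Secondary endpoints – ACT HIV, item f).** SAEs are counted to 12 months, and "Comparison of the frequency of serious adverse events between treatment groups will form an important part of the study analysis".
- **Method (Analysis of adverse events).** Fisher's test is applied to counts of patients: "The number of patients with any adverse events and specific events, respectively, will be summarised and informally compared between the two treatment arms". SAEs are one of the subgroups to be summarised separately. The others are grade 3 and 4 events, drug-related SAEs, and events that interrupt TB treatment or ART. Fatal and non-fatal SAEs are not separated in any of these places.

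The primary endpoint covers the same window: "overall survival, i.e. the time from randomisation to death, during a follow-up period of 12 months". Planned mortality is in the sample size section: "Assuming a target hazard ratio of 0.69 (corresponding to a mortality reduction from 52% to 40% in favour of dexamethasone".

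**The concern.** Safety is half of the primary aim, and endpoint f is the broadest safety endpoint in the plan. A patient counts as having an SAE if he or she dies or has a qualifying non-fatal event. With about half the placebo arm expected to die, most patients in that count are there because of the primary endpoint. The filing rule strengthens this, since it keeps all deaths but leaves out non-fatal events due only to TBM.

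Two things follow for this comparison. If dexamethasone saves lives as planned, the SAE proportion looks better on dexamethasone even with no safety advantage, and it can look neutral when non-fatal serious harm is clearly raised. If dexamethasone has no effect on survival, the deaths still dilute the contrast.

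**Working it through.** **Inputs from the protocol.** 520 patients randomised 1:1, so 260 per arm; 12-month mortality 52% (placebo) and 40% (dexamethasone); hazard ratio 0.69; 80% power at two-sided 5%; 5% loss to follow-up.

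**Assumptions.** The protocol gives no SAE rate. Let q be the 12-month risk of a non-fatal SAE, taken as independent of death, over the range 5% to 40%.

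**The plan's own figures.** Schoenfeld: 4 × (1.960 + 0.842)² / (ln 0.69)² gives 229 deaths, as stated. Mean mortality is 46%, so 229 / 0.46 = 498 patients, and 498 / 0.95 = 525, close to the stated 520. The mortality inputs can be used as given.

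**Deaths in the SAE count.** 260 × 0.52 = 135 and 260 × 0.40 = 104, together 239 before losses. All are SAE patients.

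**Make-up of the any-SAE count.** With d the mortality, P(any SAE) = 1 − (1 − d)(1 − q). The share who died is (0.52 + 0.40) divided by the sum of the two any-SAE risks. The break-even q on dexamethasone, where the any-SAE proportions are equal, is 1 − 0.48(1 − q)/0.60.

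| q, both arms | any SAE, placebo v dex | share who died | break-even q on dex (ratio to placebo) |
|---|---|---|---|
| 5% | 54.4% v 43.0% | 94% | 24% (4.8) |
| 10% | 56.8% v 46.0% | 89% | 28% (2.8) |
| 20% | 61.6% v 52.0% | 81% | 36% (1.8) |
| 30% | 66.4% v 58.0% | 74% | 44% (1.5) |
| 40% | 71.2% v 64.0% | 68% | 52% (1.3) |

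The second column shows the apparent safety advantage when non-fatal risk is identical.

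**Fisher's test on expected counts with a true non-fatal excess, placebo v dexamethasone.**

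| q | any SAE | non-fatal alone |
|---|---|---|
| 10% v 20% | 148 v 135, p = 0.29 | 26 v 52, p = 0.002 |
| 20% v 30% | 160 v 151, p = 0.47 | 52 v 78, p = 0.011 |
| 30% v 45% | 173 v 174, p = 1.00 | 78 v 117, p = 0.0006 |

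**How often each comparison signals.** Fisher's test at two-sided 5%, summed over the two binomial distributions with 260 per arm. Simulation agrees within about two percentage points.

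| mortality | q | any SAE | harm flagged, any SAE | harm flagged, non-fatal alone |
|---|---|---|---|---|
| 52% v 40% | 25% v 35% | 64% v 61% | 0.3% | 67% |
| 52% v 40% | 15% v 25% | 59% v 55% | 0.1% | 79% |
| 52% v 40% | 35% v 45% | 69% v 67% | 0.6% | 62% |
| 46% v 46% | 25% v 35% | 60% v 65% | 22% | 67% |

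With equal non-fatal risk of 25% and mortality 52% v 40%, any SAE is 64% v 55%, and Fisher's test significantly favours dexamethasone in about 52% of trials.

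**The case against.** The strongest reply is that the plan does not rest its safety conclusion on this one total.

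- The same section compares specific events one by one, counts episodes per patient with a quasi-Poisson model, and summarises drug-related SAEs, grade 3 and 4 events and events interrupting treatment. In the episode count a death does not absorb a patient's other events.
- IRIS and HIV-associated malignancy are separate endpoints with cause-specific models. Gastro-intestinal bleeding, blood sugar, Strongyloides and adrenal function have their own monitoring or ancillary studies.
- The comparisons are labelled informal.
- Filing deaths as SAEs is correct reporting practice.
- A split by outcome could sit in a full protocol or SAP that is not shown.

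Most of this stands. A reader might infer that the plan would hide an excess of non-fatal harm from dexamethasone. The document does not support that, because several other planned analyses could show it. Nor is the filing rule an error. It would also be a mistake to redefine endpoint f as non-fatal events only, since fatal drug-related harm would then leave the SAE comparison.

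The objection does not remove the point about endpoint f itself. The article fixes the filing rule, the endpoint and the method, and together they give a measure made up mostly of deaths. The other analyses are not substitutes for an overall measure of non-fatal serious harm: specific events split it into small counts, relatedness rests on a causality judgement, and grade is severity rather than seriousness, on a scale the article does not name.

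**Conclusion.** The point holds for the overall any-SAE comparison only. Over an assumed non-fatal risk of 5% to 40%, between 94% and 68% of SAE patients would be people who died. A survival benefit of the planned size would offset a non-fatal excess of 4.8-fold at a 5% placebo risk, 1.8-fold at 20% and 1.3-fold at 40%. Without a survival benefit the deaths dilute the contrast: at 25% v 35%, harm is flagged in about 22% of trials against 67%. With excess mortality on dexamethasone, deaths would add to the apparent harm.

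The non-fatal rates and their independence from death are assumptions. Positive dependence would raise the share of SAE patients who died. The figures for non-fatal SAEs alone give patients who die the same 12-month risk as survivors and use simple proportions. They show the size of the problem, not the exact gain from a time-to-event analysis. The primary analysis is unaffected. The change is worth making because this comparison is least informative in the very scenario the trial is designed to detect.

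**What to change.** Leave SAE filing and the all-SAE comparison as they are. In secondary endpoint f and in Analysis of adverse events, state that SAEs will also be compared by outcome:

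- **Non-fatal SAEs:** time from randomisation to first SAE that did not itself result in death, up to 12 months, by a cause-specific hazard model with death as a competing event. A patient who has such an event and later dies still counts. Secondary endpoint analysis already uses this type of model for IRIS and malignancy.
- **Fatal SAEs:** a table by arm, cause and assessed relatedness to study drug.

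If the full protocol or SAP already specifies this split, a cross-reference is enough. The cost is a sentence in each section, one further informal comparison and one table. Since every death and every qualifying non-fatal event is already filed on an SAE form, no new data should be needed.

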### Safety reporting

The OUCRU CTU is responsible for the reporting of SUSARs and other SARs to the regulatory authorities and the research ethics committees. The following events will be reported to the relevant authorities in Vietnam and Indonesia: All unexpected SAEs, all SAEs judged to be related or possibly related to the trial intervention, and all deaths. All SAEs will be reported to OxTREC (Oxford Tropical Research Ethics Committee) in the annual review form and to the DMC in accordance to the DMC charter. An independent DMC will oversee the safety of the trial.

### Interim analyses

Interim analyses are planned after 6 and 12 months of recruitment and yearly thereafter until the completion of the trial but the DMC has the authority to modify the frequency of interim analyses. At these interim analyses, the DMC will receive a report including unblinded summaries of baseline characteristics, the primary endpoint, and adverse events by treatment arm. The DMC will also review data from those enrolled into the DILI strategy ancillary study, in particular the incidence of acute hepatic failure in each of the management strategy arms.

## Statistical analysis

### Sample size justification – ACT HIV (main trial)

A previous trial of dexamethasone included 545 subjects with TBM and reported a reduced risk of death by 9 months associated with dexamethasone (hazard ratio of death 0.69 (95% CI 0.52–0.92)) and no evidence of heterogeneity with respect to HIV status though the number of HIV-infected patients was low (98 subjects) and none of them received antiretroviral therapy
^8^. A recent TBM trial of intensified TBM treatment reported 9-month mortality in 349 HIV-infected patients of 40% in both study arms and all subjects received dexamethasone
^7^. Few additional deaths are expected to occur between months 9 and 12
^15^. Assuming a target hazard ratio of 0.69 (corresponding to a mortality reduction from 52% to 40% in favour of dexamethasone), a total of 229 deaths need to be observed during the 12-month follow-up duration to obtain a power of 80% at the two-sided 5% significance level according to Schoenfeld’s formula. To achieve this and allowing for a 5% loss-to-follow-up, a total of 520 HIV-infected subjects with TBM need to be recruited into the main trial.

### Sample size justification – DILI strategy study

A review of 36 subjects who interrupted rifampicin and isoniazid because of clinical hepatitis or jaundice events from our previous trial
^7^ gave the following data: the median (IQR) onset date of the DILI was 50 (15–84) days from initiation of anti-tuberculosis treatment, the median (IQR) duration of the rifampicin and isoniazid interruption was 16 (12–24) days, and 12 subjects subsequently died (8 of them within 60 days). Of note, the duration of the treatment interruption was <30 days for 32 (89%) of the 36 subjects and the remaining 4 subjects never re-started rifampicin or isoniazid but continued to receive alternative anti-tuberculosis treatment for >100 days. For the DILI strategy study we hypothesise that strategies 1 and 2 will result in a relative reduction in the duration of the treatment interruption of 50% for subjects with interruptions <30 days, but that they do not affect longer interruptions (as the corresponding subject might have permanent intolerance to rifampicin and isoniazid) or mortality. Based on simulations of hypothetical trials using re-sampling from the data described above, the hypothesised treatment effect, and the Wilcoxon rank sum test for analysis, we determined that the power to detect such an effect size with a sample size of at least 50 subjects per arm is >85%. Of note, given this is an ancillary and essentially ‘opportunistic’ study, we have chosen a liberal (i.e. not multiplicity corrected) two-sided significance level of 5% for each of the two primary comparisons of strategies 1 and 2, respectively, versus strategy 3. A total of 170 participants will be recruited to the DILI sub-study. The DILI sub-study has been powered for the combined analysis of ACT HIV (we anticipate 100 ACT HIV patients will consent to the DILI sub-study) and LAST ACT (a linked RCT of dexamethasone in HIV-uninfected adults with TBM stratified by LTA4H genotype, from which we anticipate 70 patients will enter the DILI sub-study)
^22^.

### Analysis populations – ACT HIV (main trial)

Patients in the main trial will be analysed according to their randomised arm as an intention-to-treat (ITT) analysis. In addition, the primary endpoint will be analysed in the per-protocol population, which will exclude the following patients: patients with a final diagnosis other than TBM, major protocol violations and those receiving less than 1 week of administration of the randomised study drug for reasons other than death. Published diagnostic criteria
^23^ will be applied to all enrolled participants at the end of the study when all mycobacterial culture results are available (
Supplementary File 4). The criteria will sub-divide all cases into definite, probable and possible TBM, and those with an alternative diagnosis.

For the primary analyses of the main trial the second randomisation in the DILI strategy study will be ignored and the estimated dexamethasone treatment effect can thus be interpreted as an average effect across these three management strategies. We believe that this is justified because only approximately 100 (19%) subject are expected to be enrolled in the nested trial with roughly similar numbers from both arms, because the efficacy of the different management strategies is unlikely to depend on whether the patient received dexamethasone or not as it tests a very different intervention, and because the anticipated effect of the management strategy on survival is relatively small. However, in a supplementary analysis, we will also compare the primary endpoint between the treatment policies “dexamethasone treatment plus standard of care management of drug-related liver injury” vs. “placebo treatment plus standard of care management of drug-related liver injury” using an inverse probability weighting based analytical framework
^24^.

### Analysis populations – DILI strategy study

All patients in the DILI strategy study will be analysed according to their randomised arm as an ITT analysis. The two primary comparisons are the comparisons of strategies 1 and 2, respectively, versus strategy 3 (with tests conducted at the unadjusted two-sided 5% significance level) and comparisons between strategies 1 and 2 will be exploratory only.

### Primary endpoint analysis – ACT HIV (main trial)

The primary endpoint of the main trial is overall survival, i.e. time from randomisation to death, during 12 months of follow-up. Overall survival will be analysed with a Cox proportional hazards regression model with treatment as the only co-variate and stratification by TBM MRC severity grade at enrolment (I, II, or III) and country (Vietnam or Indonesia). The primary effect measure is the resulting hazard ratio comparing dexamethasone vs. placebo with a corresponding two-sided 95% confidence interval and p-value. The significance level of the associated two-sided test will be set to 5%. Kaplan-Meier plots and explicit survival estimates at 3, 6, 9, and 12 months of follow-up will also be calculated for the full populations and in the subgroups defined by TBM disease severity and country separately. The proportional hazards assumption will be formally tested based on scaled Schoenfeld residuals and visually assessed by a plot of the scaled Schoenfeld residuals versus transformed time. In case of a significant test, a formal comparison of the absolute risk of death at 12 months between the two groups will also be performed (using a Wald-type test based on Kaplan-Meier estimates at 12 months and associated standard errors using Greenwood’s formula).

The homogeneity of the treatment effect on overall survival across subgroups will be assessed by subgroup analyses and formal tests of interaction between treatment and the following grouping variables: TBM MRC severity grade at enrolment (I, II, or III), country (Vietnam or Indonesia), drug resistance pattern (MDR-TB or rifampicin mono-resistance, isoniazid resistant non-MDR, no or other resistance), ART status at enrolment (ART naive, ≤3 months of ART, >3 months of ART), and CD4 cell count at enrolment. To obtain an adjusted treatment effect estimate and to assess the effect of other covariates on survival, the primary endpoint will also be modelled using a multivariable Cox proportional hazards regression model including the following covariates (in addition to the treatment group): TBM MRC severity grade at enrolment, country, drug resistance pattern, ART status and CD4 cell count at enrolment. Multiple imputation will be used to handle missing covariates.

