### HIV monitoring

HIV infection must be confirmed before entry to the study. Peripheral blood CD4 count and HIV viral load will be measured at baseline (routine counts taken within 2 weeks of study entry are acceptable), and CD4 count will be repeated at 60 days.

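### Adding CD4 count and ART status at enrolment to the primary Cox model would probably raise power at little cost; the planned model is valid, so this is an improvement and not a correction

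*Protocol article*

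**What the plan says.** The section on the primary endpoint analysis of the main trial states: "Overall survival will be analysed with a Cox proportional hazards regression model with treatment as the only co-variate". The same sentence goes on to add "stratification by TBM MRC severity grade at enrolment (I, II, or III) and country (Vietnam or Indonesia". This model supplies the primary hazard ratio and the two-sided 5% test.

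The next paragraph of that section adds a second model of the same endpoint: "the primary endpoint will also be modelled using a multivariable Cox proportional hazards regression model". Its covariates besides treatment are "TBM MRC severity grade at enrolment, country, drug resistance pattern, ART status and CD4 cell count at enrolment". Its purpose is given as "To obtain an adjusted treatment effect estimate and to assess the effect of other covariates on survival", and the paragraph ends: "Multiple imputation will be used to handle missing covariates". ART status has three levels (none, up to 3 months, more than 3 months). ART status and CD4 count are also subgroup factors.

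Under HIV monitoring: "Peripheral blood CD4 count and HIV viral load will be measured at baseline". Under Randomisation, the allocation strata are site and MRC grade only.

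**The concern.** The plan treats CD4 count and ART status as relevant to survival, yet keeps both out of the model that decides the trial. Neither the randomisation strata nor the primary analysis takes them into account.

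In a Cox model this matters even when the arms are perfectly balanced. Omitting a covariate that predicts death draws the treatment hazard ratio towards 1. The standard error barely changes, so power falls. The margin is thin: 80% power holds at a hazard ratio of 0.69 and drops quickly for smaller effects. Baseline data that are already planned could recover some of the loss without recruiting more patients.

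**Working it through.** **Inputs from the documents.** Sample size justification (main trial): hazard ratio 0.69, 12-month mortality 52% v 40%, power 80%, two-sided 5%, 229 deaths, 5% loss, 520 participants. Design and setting: 1:1 allocation. Primary endpoint analysis: 3 MRC grades × 2 countries = 6 strata.

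**Step 1: the plan's own figure.** Schoenfeld: deaths = 4(1.960 + 0.842)² / (ln 0.69)² = 228.02, rounded up to 229. This reproduces.
- Power with 229 deaths: Φ(√229/2 × 0.371 − 1.960) = 80.2%.
- Participants: 229/0.46 = 498, and after 5% loss about 525, against 520 planned.
- In reverse: 520 × 0.95 × 0.46 = 227 deaths, power 79.9%.

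The planned power does not depend on covariate adjustment.

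**Step 2: the margin.** The same formula with 229 deaths gives 59% power at a hazard ratio of 0.75 and 39% at 0.80.

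**Step 3: gain from adding CD4 and ART status.** Trials of 520 patients were simulated and analysed twice: with the planned model (6 strata, treatment only), and with the same model plus CD4 and three-level ART status.

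Assumptions not in the documents:
- MRC grades 30/45/25%, with log hazards −0.7, 0 and 0.7
- 70% of patients in Vietnam, country log hazard ratio 0.2
- ART levels 50/25/25%
- CD4 on a standardised scale, independent of MRC grade and ART
- Weibull hazard with shape 0.6, so deaths come early
- control mortality set near 52%, and 5% lost at random times

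The prognostic hazard ratio in the first column applies per SD of CD4 and to the extreme ART levels; the other ART level lies halfway on the log scale.

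Setting A (2,500 trials per row) holds the adjusted treatment hazard ratio at 0.69. Setting B (4,000 per row) chooses it so that the planned model sees about 0.69, as the sample size assumes. Gains are taken before rounding.

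| Prognostic HR | A: planned | A: adjusted | Gain | B: planned | B: adjusted | Gain |
|---|---|---|---|---|---|---|
| 1.0 | 80.5% | 80.6% | 0.1 | not run | not run | |
| 1.2 | 78.1% | 79.4% | 1.4 | 80.7% | 81.8% | 1.1 |
| 1.3 | 78.2% | 79.9% | 1.6 | 78.0% | 80.3% | 2.4 |
| 1.5 | 74.8% | 79.8% | 5.0 | 81.0% | 85.0% | 4.0 |
| 1.8 | 69.4% | 79.6% | 10.2 | 78.8% | 88.3% | 9.5 |

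Read along rows, not down columns. The simulation standard error of a single power is about 0.6 to 0.8 points, and in B the hazard ratio seen by the planned model varied from 0.686 to 0.696 between rows. Both models were fitted to the same data sets, so the differences are firmer than the levels.

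**Step 4: hand check of one row.** Setting A at 1.5: the planned model averages a hazard ratio of 0.704 with standard error 0.1323, so |ln 0.704|/0.1323 = 2.65 and power is Φ(2.65 − 1.96) = 75.5%. The adjusted model averages 0.688 with 0.1333, giving 2.80 and Φ(2.80 − 1.96) = 80.0%. The gain comes from the hazard ratio, not from the standard error.

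**Step 5: type I error.** With no treatment effect, rejection rates were 5.0% to 5.5% (planned) and 5.1% to 5.4% (adjusted).

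**The case against.** The case for leaving the model alone is strong. It is unambiguous. Its strata follow the randomisation for MRC grade and, at a coarser level, for site. It matches the unadjusted sample size calculation, holds its error rate and meets its stated power. The adjusted estimate is already prespecified with multiple imputation and will be reported. Nothing in the documents shows how strongly CD4 or ART status predicts death. Moving them into the primary test also brings in a functional form and a missing-data rule that the planned test does not need. All of this stands, and it makes the point a matter of efficiency. What it leaves untouched is that the secondary model does not carry the 5% test, so its extra power does not help the trial's main conclusion.

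A reader might infer more than the documents support:
- *That the primary analysis ignores prognosis.* It does not; MRC grade and country are already strata.
- *That the trial is underpowered because of the omission.* Step 1 shows the stated power is met.
- *That the gain is free.* It is cheap, but the hazard ratio changes meaning and missing values must be handled.
- *That the hazard ratio of 0.86 in the HIV-infected subgroup of the earlier trial makes adjustment necessary.* The article gives its interval as 0.52 to 1.41, which includes 0.69, and reports no clear heterogeneity. Adjustment would not rescue that case either. Power with 229 deaths at 0.86 is about 21%. The gain at a prognostic hazard ratio of 1.5 (setting B) is worth ((1.96 + 1.034)/(1.96 + 0.876))² = 1.11, or 11% more deaths. With 229 × 1.11 = 254 deaths, power is about 22%.
- *That two models which may fall on either side of 0.05 are a defect.* Naming one as primary settles this, and the same possibility remains after the change.

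**Conclusion.** The point holds as a low-cost improvement and not as an error. The planned primary model is valid and delivers about 80% power at 0.69. Adding CD4 count and ART status would probably raise power: by about 0 to 2 points if they are weakly prognostic, 4 to 5 points at a hazard ratio of 1.5, and 9 to 10 points at 1.8. These figures rest on assumed prognostic strengths and on the mix of grades, countries and ART levels in the working. They also assume CD4 is independent of MRC grade; if the two are correlated, the strata already absorb part of the effect and the gain is smaller. If neither variable predicts death, the gain is nil, and the simulation shows no material loss.

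**What to change.** Before unblinding, and without sight of the unblinded interim reports, define the primary model as the stratified Cox model with treatment, CD4 count at enrolment in a prespecified form (for example log) and three-level ART status at enrolment. Prespecify a rule for missing CD4 that uses baseline information only, so that neither outcome nor allocation enters it. Report the treatment-only stratified model as supportive. Leave drug resistance in the secondary multivariable model.

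The cost is a change of wording in the analysis plan; no new data are needed. There are two downsides. The primary hazard ratio becomes conditional on CD4 and ART status: in setting B it averaged 0.67 against 0.69 at a prognostic hazard ratio of 1.5, and 0.66 against 0.69 at 1.8. A missing-data rule also becomes part of the primary test.
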